**Table 1 Tab1:**
[figure not shown]
Schedule of enrollment, intervention, and assessments

There will be five visits for each participant in week 0, week 4, week 12, week 24, and week 28. At the first visit, patients will have their general data recorded and will be given the prescription. Then, patients will take the prescription to the specified pharmacy and receive either Yirui capsules or the placebo. 4 weeks and 12 weeks after the first visit, patients will come back for clinical evaluation and medication. Visit 4 is planned for the end of the treatment period (week 24); at this visit patients will only receive clinical evaluation. Afterwards, the patients will stop taking Yirui capsules or the placebo for another 4 weeks and then come back for clinical evaluation.

The study protocol was approved by the ethics committees of the First Affiliated Hospital of Jinan University, Guangdong No. 2 Provincial People’s Hospital, Hexian Memorial Affiliated Hospital of Southern Medical University, and the Fifth Affiliated Hospital, Sun Yat-sen University (Approval Version: LWXJ.YRJN-HBT-V1.0), and informed consent was obtained from each participant.

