### Outcomes

Clinical investigators will obtain written informed consent and collect basic data such as gender, age, height, weight, and medical history at baseline. For safety concerns, besides the basic data, vital signs will be taken and laboratory examinations conducted, for instance, blood pressure, heart rate, routine blood tests (e.g., red blood cell (RBC), white blood cell (WBC), hemoglobin (Hb), etc.), liver and kidney function tests (e.g., ALT, AST, CREA, etc.), pregnancy test, and 12-lead electrocardiogram (ECG). Except for the pregnancy test, which only needs to be conducted in the first visit (week 0, baseline), other tests should be conducted routinely at every visit during the treatment period (the ECG is not mandatory at the second visit (week 4)). Also, any adverse events such as abdominal discomfort should be monitored and recorded during the whole study.

Participants need to receive a blood lipid profile test which contains the following indexes: TC, TG, HDL-C, LDL-C, apolipoprotein A (apoA), apolipoprotein B (apoB), and non-high-density lipoprotein cholesterol (non-HDL-C). The blood sample should be collected after at least a 12-hour fast, and the last meal before the blood sampling should not contain greasy food. In order to evaluate the health status of participants, the MOS 36-Item Short-Form Health Survey (SF-36) is utilized [26–28]. In addition, for assessment of clinical symptoms, another symptomatic grading and quantifying scale is applied. Weight monitoring and diet evaluation are also two aspects that need to be conducted. All participants are required to complete the tests and scales mentioned above at every visit under the guidance and assistance of the clinical investigators. The results are recorded and compared within a group and between groups before and after intervention.

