Yirui capsules are designed to act as an intervention method for patients with borderline high serum lipid or an adjunctive choice for patients who could not reach the serum lipid target with conventional therapy. Based on the 2013 American College of Cardiology (ACC)/American Heart Association (AHA) guidelines on the treatment of blood cholesterol [29], the 2007 Chinese guidelines on blood lipid abnormality [30], and a previous TCM clinical trial [31], we set the treatment goal as a 30 % LDL-C decline compared with baseline after intervention. Therefore, the primary outcome is the percentage of participants who reach the goal at treatment endpoint (week 24). Secondary outcomes include the mean changes from baseline at treatment endpoint in LDL-C, TC, TG, HDL-C, apoA, apoB, non-HDL-C, SF-36 scoring, total and individual item scoring of symptomatic grading and quantifying scale, and body mass index (BMI).

Safety and tolerability assessments include collection of adverse events, physical examination, vital signs, and the relevant laboratory examination reported previously. Clinical investigators should observe any adverse events that occur during the clinical trial, including abnormal symptoms and signs, unusual laboratory indicators, etc. Whether or not the adverse event is related to the interventions, investigators are required to record it comprehensively, including onset time, related symptoms and signs, extent, duration, laboratory indexes, treatment, result, and follow-up. In addition, drug combinations should also be documented in order to analyze the correlation between adverse events and experimental products.

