### Statistical analysis

All effectiveness and safety evaluations will be conducted according to the intention-to-treat (ITT) principle. The last-observation-carried-forward method will be applied to deal with missing values. SAS (Version 9.2) will be utilized to analyze the data, and the statistical significance is defined as a two-sided *P* value of <0.05. For measurement data, the mean, standard deviation (SD), maximum, minimum, P25, median, and P75 will be reported. For paired measurement data, the mean difference, SD, and confidence interval (CI) will also be reported. As to enumeration data and ranked data, frequency distribution and corresponding percentage are compulsory. Baseline data of the two arms (e.g., demographic data) will undergo descriptive and inferential analyses. Intra-group efficacy comparisons before and after the treatment will be conducted by using the paired *t* test or Wilcoxon signed rank test for quantitative variables and the chi-squared test for qualitative variables. Efficacy difference between groups will be assessed with the utilization of the two-sample *t* test or corresponding non-parameter methods for quantitative variables, the chi-squared test for qualitative variables, and the Wilcoxon rank sum test for rank variables. For the primary outcome, the mean difference with two-sided 95 % CI will be reported. Statistic effectiveness is defined as the lower limit of 95 % CI above 0. Clinical effectiveness needs to be assessed after combining with clinical significance. For the consideration of the multicenter character, a covariance model is used to evaluate the center effect for the primary variable. Other secondary outcomes will take no account of the center effect. In addition, the chi-squared test will be utilized to analyze the rate of adverse events between the two arms. A table will be generated to enumerate and describe the characters of all adverse events during the study.

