### Data collection and handling of withdrawal and dropout

In this 28-week clinical trial, it is compulsory for participants to take experimental medication for a continuous 24 weeks, be present at five assessment visits, conduct several blood tests, finish certain scales, complete a diet evaluation diary card, and stop taking other lipid-lowering medication and drugs with relevant herbal ingredients. Specially assigned individuals will record the original data, and the relevant materials will be placed on file based on numerical order at the specified site appropriately. Only principal investigators and clinical investigators have the right to examine the documents. Original documents should be preserved at least 5 years after finishing the study.

For maximum compliance of patients, we require all researchers and doctors to obey the following rules. Firstly, all researchers should obey the principle of informed consent and help participants understand the requirements of the study. Secondly, researchers need to monitor the compliance of patients through the dose counting method. Thirdly, all doctors should ask patients to bring all medications to every visit to examine and record any drug combinations. Moreover, investigators will contact the participant to remind them of the visit three days in advance and to inform them of the specific arrangements for the next visit. For patients who do not respond to the medication or cannot take medication on time, increasing the frequency of the follow-up visits is compulsory.

Participants can quit the study if they experience: (1) severe adverse effect(s), (2) hypersensitivity towards the research medication, or (3) aggravation of disease. The whole research plan will be terminated for the following circumstances: (1) presence of serious adverse events related to the research medication, (2) no practical value findings of the medication during the treatment, or (3) completion of all follow-up assessments.

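### Carrying the last LDL-C forward scores some dropouts as week-24 responders, which can bias the primary comparison in a direction and by an amount the protocol does not fix

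*Protocol article*

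**What the plan says.** - Missing data (Protocol article, Statistical analysis): "The last-observation-carried-forward method will be applied to deal with missing values". The sentence before it reads "All effectiveness and safety evaluations will be conducted according to the intention-to-treat (ITT) principle". The section gives no separate rule for the primary outcome.
- Primary outcome (Outcomes): "we set the treatment goal as a 30 % LDL-C decline compared with baseline after intervention", and hence "the primary outcome is the percentage of participants who reach the goal at treatment endpoint (week 24").
- Visits (Study design, text after Table 1): "There will be five visits for each participant in week 0, week 4, week 12, week 24, and week 28". Capsules stop at week 24.
- Lipids between baseline and week 24 (Outcomes): "All participants are required to complete the tests and scales mentioned above at every visit". The blood lipid profile is among those tests.
- Withdrawal (Data collection and handling of withdrawal and dropout): "Participants can quit the study if they experience: (1) severe adverse effect(s), (2) hypersensitivity towards the research medication, or (3) aggravation of disease". The section does not provide for a week-24 lipid sample after withdrawal.
- Expected dropout (Sample size calculation): about 20 %, giving 90 per group, with planning rates of 30 % on Yirui and 10 % on placebo.

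**The concern.** Read together, these statements decide how a dropout is scored. Someone whose LDL-C has fallen 30 % by week 4 or week 12 and who then leaves has that value moved to week 24 and counts as a success, up to 20 weeks after the last measurement. The protocol gives no evidence that a lipid effect lasts once capsules stop.

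The reasons listed for leaving (severe adverse effects, hypersensitivity, aggravation of disease) can be related to treatment and can differ by arm. If they do, or if early falls are commoner among dropouts in one arm, the carried values do not cancel between arms. Success is declared when the lower 95 % confidence limit exceeds 0, so for roughly a fifth of participants that decision could rest on the imputation rule. This is a stated rule, not a detail left to an unseen analysis plan; a plan that followed the article would inherit it.

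**Working it through.** **Inputs from the protocol.** 90 per arm; dropout about 20 %; planning rates 30 % and 10 %; carry-forward from weeks 0, 4 and 12; two-sided 5 % test, which is 2.5 % in favour of Yirui.

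**Inputs assumed, because the protocol does not give them.** The split of dropout by arm, the share of dropouts with a post-baseline lipid value, and the share of those at goal at their last visit.

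**The plan's own figures.** 75 × 1.2 = 90 per group. The printed sample size formula gives (0.09 + 0.21)/0.04 × 10.5 = 78.75 rather than 75; that is a separate matter and does not affect this point. Dropouts: 0.20 × 90 = 18 per arm. If 30 % and 10 % of them were at goal when last seen, 5.4 and 1.8 of them are scored as week-24 responders.

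**Formulas.** For one arm, let q be the response rate among completers, d the dropout rate, f the share of dropouts with a post-baseline value, and r the response rate at the last visit among those. A dropout before week 4 carries baseline forward and is a non-responder.

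- Carry-forward rate: (1 − d)q + d·f·r
- Missing counted as non-response: (1 − d)q

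Rejection rates below are for the pooled two-proportion z test (z > 1.96) at 90 per arm.

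**A. No week-24 difference among completers (q = 10 % in both arms), carry-forward analysis**

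| Dropout Yirui/placebo | r Yirui vs placebo | f | Analysed rates | False positive for Yirui |
|---|---|---|---|---|
| 20/20 % | 10 vs 10 % | 1 | 10 vs 10 % | 2.5 % |
| 20/20 % | 20 vs 10 % | 1 | 12 vs 10 % | 6.3 % |
| 20/20 % | 30 vs 10 % | 0.5 | 11 vs 9 % | 6.5 % |
| 20/20 % | 30 vs 10 % | 1 | 14 vs 10 % | 13 % |
| 30/10 % | 30 vs 10 % | 1 | 16 vs 10 % | 22 % |

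Fourth row: 0.8 × 10 + 0.2 × 30 = 14 % against 0.8 × 10 + 0.2 × 10 = 10 %.

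**B. The same null, missing counted as non-response**

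| Dropout Yirui/placebo | Analysed rates | False positive for Yirui |
|---|---|---|
| 20/20 % | 8 vs 8 % | about 2.5 % |
| 30/10 % | 7 vs 9 % | 0.7 % |
| 10/30 % | 9 vs 7 % | about 7 % |

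**C. Completers at 30 % vs 10 %, f = 1: difference in points**

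| Dropout Yirui/placebo | r Yirui vs placebo | Carry-forward | Missing = non-response | Gap |
|---|---|---|---|---|
| 20/20 % | 30 vs 10 % | 30 − 10 = 20 | 24 − 8 = 16 | +4 |
| 30/10 % | 30 vs 10 % | 30 − 10 = 20 | 21 − 9 = 12 | +8 |
| 20/20 % | 10 vs 10 % | 26 − 10 = 16 | 24 − 8 = 16 | 0 |
| 10/30 % | 10 vs 10 % | 28 − 10 = 18 | 27 − 7 = 20 | −2 |

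The gap equals bias only if every dropout is truly below goal at week 24.

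**Power at 90 per arm, 20/20 % dropout.** About 93 % for 30 % vs 10 % (first row of C, carry-forward) and about 85 % for 24 % vs 8 % (missing as non-response). The normal approximation gives 92.5 % and 83.9 %.

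**The case against.** The strongest reply is that the larger error rates come from the assumptions. The protocol reports no early response rate, no sign that an effect is transient, and one dropout figure not split by arm or by reason. The 13 % and 22 % need a 30 % early response among Yirui dropouts that is absent at week 24 among completers. Early leavers carry baseline forward and cannot be false successes, and people who leave because their disease worsens would tend to carry a non-response. Table C takes non-response as the truth and then measures carry-forward against it. All of this stands. It limits what can be said about size and direction, but it does not remove the mechanism.

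Non-response imputation is not neutral either: table B shows about 7 % when placebo dropout is the higher. That stands too, and is why sensitivity analyses belong in the fix.

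A reader might also infer three things that the document does not support:
- That carry-forward is prescribed for all safety evaluations. The words about effectiveness and safety belong to the intention-to-treat sentence; the next sentence refers only to missing values, and adverse events are compared as rates and listed.
- That understated standard errors count against carry-forward in particular. Any single imputation treats imputed values as observed, including counting missing as failure.
- That every carried value comes from someone off treatment. A week-24 visit missed while still taking capsules is handled the same way.

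**Conclusion.** The point holds in a conditional form. The stated rule allows a week-4 or week-12 fall to be scored as week-24 response for participants who have stopped, and with 18 expected dropouts per arm this can distort the primary comparison if dropout or carried-forward response differs by arm.

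It would be tempting to conclude that the rule does bias the result towards Yirui. The document does not support that. Across the scenarios shown, the false-positive rate runs from nominal to 22 %, and the gap in the estimated difference from −2 to +8 points, including zero. Equal dropout alone does not protect the trial, since the 6 % and 13 % figures arise at 20 % in both arms. All of these rates rest on assumed early response and dropout patterns and should be read as a range, not a forecast.

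**What to change.** - **Primary analysis.** Replace carry-forward for the primary outcome: analyse all randomised participants and count a missing week-24 LDL-C as not reaching the goal.
- **Data collection.** Where a participant stops capsules but consents to remain, still take the scheduled week-24 lipid sample, so that fewer outcomes need imputing.
- **Sensitivity analyses.** Because the new rule can favour Yirui if placebo dropout is higher, pre-specify multiple imputation using arm, centre and baseline, week-4 and week-12 LDL-C, and a tipping-point analysis.

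The rule should be fixed before unblinding. The cost is a change of wording, modest programming, and power of about 85 % instead of 93 % at 90 per arm under 20 % dropout and 30 % versus 10 % among completers.

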## Methods/design

### Study design

This study is conducted as a double-blind, placebo-controlled trial with two parallel groups to examine the blood lipid-lowering effect of Yirui capsules. The protocol was developed according to Consolidated Standards of Reporting Trials (CONSORT) statement [22], Standard Protocol Items: Recommendations for Interventional Trials (SPIRIT) 2013 [23], and SPIRIT 2013 explanation and elaboration: guidance for protocols of clinical trials [24]. We plan to recruit 180 patients from the First Affiliated Hospital of Jinan University, Guangdong No. 2 Provincial People’s Hospital, Hexian Memorial Affiliated Hospital of Southern Medical University, and the Fifth Affiliated Hospital, Sun Yat-sen University. Clinical investigators from each center are responsible for screening eligible participants. After recruitment, participants are randomly and equally divided into two groups, the Yirui capsule group and the placebo group. Both arms will receive lifestyle modification therapy (decreasing the intake of saturated fatty acids and cholesterol, selecting foods which could reduce LDL-C, losing weight, increasing regular physical exercise, quitting smoking, limiting salt intake, etc.). Based on lifestyle modification, the Yirui group will receive Yirui capsules while the placebo group will receive simulant capsules. Then, the two arms will undergo a 24-week treatment and 4-week follow-up period. According to the China Food and Drug Administration guidelines [25], this 24-week treatment period was set based on our clinical experience and previous pilot studies. The participant flowchart is shown in Fig. 1, and the participant timeline is given in Table 1.

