#### Inclusion criteria

In this study, the inclusion criteria are as follows: (1) age of 18 to 65 years, both genders; (2) documented blood lipid test results indicated LDL-C ≥3.37 mmol/L complicated with TC ≥5.18 mmol/L, or triglyceride (TG) ≥1.70 mmol/L, or high-density lipoprotein cholesterol (HDL-C) <1.04 mmol/L, or both TC ≥5.18 mmol/L and TG ≥1.70 mmol/L; (3) initial treatment of hyperlipidemia; (4) signed informed consent and agreement to complete all visits, examinations, and treatments.

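### Within-arm before-after tests are labelled as efficacy comparisons although they cannot isolate a capsule effect, and paired qualitative data are given a chi-squared test that, as written, ignores the pairing

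*Protocol article*

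**What the plan says.** The relevant sentence in the Statistical analysis section of the protocol article begins "Intra-group efficacy comparisons before and after the treatment will be conducted by using the paired" (the t test is meant) and offers as alternatives the "Wilcoxon signed rank test for quantitative variables and the chi-squared test for qualitative variables". The Outcomes section plans the same kind of comparison: "The results are recorded and compared within a group and between groups before and after intervention". Neither section calls the within-arm tests descriptive or bars efficacy conclusions from them.

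The next sentence of the Statistical analysis section covers the comparison between arms: "Efficacy difference between groups will be assessed with the utilization of the two-sample" t test or a non-parametric counterpart, chi-squared for qualitative variables, and the rank sum test for rank variables. A success rule follows, for the primary outcome only: "Statistic effectiveness is defined as the lower limit of 95 % CI above 0".

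Two design features bear on this. Under Study design, "Both arms will receive lifestyle modification therapy". Under Inclusion criteria, participants enter on abnormal lipid values; one route is "documented blood lipid test results indicated LDL-C ≥3.37 mmol/L" together with raised total cholesterol.

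**The concern.** There are two separate problems, and they act in different directions.

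First, a before-after test inside one arm measures everything that changed over 24 weeks: diet, exercise, weight loss, regression to the mean after selection on an abnormal value, and any capsule effect. It cannot separate the last of these from the rest, which is why the trial has a placebo arm. Calling the test an efficacy comparison invites a reader, or the authors, to treat a small P value in the Yirui arm as evidence for the capsule. The secondary list is long (seven lipid measures, SF-36, total and individual symptom scores, BMI), and no stated rule says those claims must rest on the between-arm difference.

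Second, before and after values of a qualitative variable come from the same people. The sentence respects this for quantitative variables but then gives qualitative variables the test that the following sentence uses for two independent arms. Read as the ordinary Pearson test, it uses the wrong variance.

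**Working it through.** The plan gives no figure on this point to reproduce. From the documents come 90 participants per arm (Sample size calculation) and a two-sided 0.05 level (Statistical analysis). The drifts, correlations and illustrative counts below are assumptions, because the documents supply none.

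**1. Within-arm test with an inert capsule.** Let d be the mean fall from lifestyle change and regression to the mean, in units of the SD of the change. The paired t statistic then follows a noncentral t distribution with 89 degrees of freedom and noncentrality d × √90 = 9.487d. The chance of a significant fall is the probability that this exceeds the critical value of about 1.987.

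| Assumed drift d | Noncentrality | P(significant fall) |
|---|---|---|
| 0 | 0 | 0.025 |
| 0.1 | 0.95 | 0.15 |
| 0.2 | 1.90 | 0.47 |
| 0.3 | 2.85 | 0.80 |
| 0.5 | 4.74 | 0.997 |

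With 75 participants the range for d = 0.1 to 0.5 is 0.135 to 0.990, so the result hardly depends on dropout.

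**2. One arm significant, the other not.** If both arms drift by the same 0.2 SD and the capsule does nothing, the chance that only the Yirui arm reaches significance is p(1 − p) = 0.467 × 0.533 = 0.25.

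**3. Chi-squared on paired data: one illustrative table.** Take 90 participants: symptom present at both times in 40, before only in 14, after only in 3, at neither time in 33. The margins are 54/90 before and 43/90 after.

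- Ordinary chi-squared: pooled proportion 97/180 = 0.539; standard error √(2 × 0.539 × 0.461 / 90) = 0.0743; z = (11/90)/0.0743 = 1.64; P = 0.10.
- Exact McNemar on the 17 discordant pairs: 2 × (1 + 17 + 136 + 680)/2^17 = 1668/131072; P = 0.013.

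The tests differ because the ordinary one omits the covariance between the two measurements. The pre-post correlation in this table is (40 × 33 − 14 × 3)/√(54 × 36 × 43 × 47) = 0.64.

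**4. Chi-squared on paired data: general behaviour.** Simulation with 100,000 runs, 90 pairs, baseline proportion 0.5, nominal level 0.05 and no true change:

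| Pre-post correlation | Type I error, ordinary chi-squared | Type I error, McNemar |
|---|---|---|
| 0 | 0.044 | 0.049 |
| 0.3 | 0.017 | 0.052 |
| 0.5 | 0.005 | 0.054 |
| 0.7 | 0.0004 | 0.045 |

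For a true 15-point fall at correlation 0.5, power is 0.54 with the ordinary test and 0.84 with McNemar.

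**5. Which endpoints are exposed.** The primary outcome is the proportion reaching a 30% LDL-C decline. It is defined by change from baseline, so it has no before value and no within-arm before-after test applies. The secondary outcomes are mean changes or scores. Individual symptom items are the likeliest to be analysed as categories. The between-arm sentence has a separate class for rank variables and the within-arm sentence does not, so a graded item could fall under the qualitative heading there.

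**The case against.** The strongest reply is that no conclusion in the plan is tied to a within-arm test. Between-group tests are specified in the very next sentence, and the primary success rule, read in sequence, concerns the difference between arms. This stands. A reader might infer that the trial could declare an inert capsule effective on its primary outcome; the documents do not support that.

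A second tempting inference is that the chi-squared error helps the capsule look effective. It does the opposite: with positive pre-post correlation the ordinary test gives P values that are too large. It is a fault in its own right and adds nothing to the first problem.

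Third, the wording may be shorthand. McNemar's test is itself a chi-squared test for paired proportions, and the authors recognised the pairing for quantitative variables. That is possible, but the text does not say so, and it uses the same test name for independent arms. An analyst following it would reasonably run the ordinary test.

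Fourth, the size of the drift is assumed, and improvement in each arm is not certain. Some entry routes do not require raised LDL-C, which weakens regression to the mean for LDL-C in those participants. Both points are fair, and they are why a wide range is shown. They do not rescue the within-arm test, which cannot separate the capsule from the background whatever the drift. The plan itself assumes a placebo effect of about 10%.

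Finally, part of the remedy is already planned: for paired measurement data the mean difference, SD and confidence interval are to be reported.

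**Conclusion.** The point holds, with limited reach. The plan gives an efficacy label to within-arm tests that cannot support one. Under an assumed drift of 0.1 to 0.5 SD of the change, an arm of 90 taking an inert capsule would show a significant fall in about 15% to over 99% of trials. The plan also names a test for before-after qualitative data that, read as the ordinary chi-squared, ignores the pairing and is conservative: at an assumed correlation of 0.5, type I error is 0.005 and power 0.54 against 0.84 for McNemar. That second fault matters mainly for symptom items analysed as categories.

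The primary analysis is untouched. What is exposed is the interpretation of secondary and supportive results, for which no rule ties efficacy claims to the comparison between arms. It should be corrected, but it does not threaten the trial's main conclusion.

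**What to change.** Three changes of wording in the Statistical analysis section, or in the SAP:

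1. State that efficacy, for all outcomes and not only the primary, is concluded solely from between-group comparisons.
2. Drop the efficacy label from the within-arm comparisons and report them descriptively. For paired measurement data the planned mean difference with its confidence interval already does this.
3. If a before-after test of a qualitative variable is kept, replace chi-squared with McNemar for two categories, Wilcoxon signed rank for ordered categories, or Bowker or another marginal homogeneity test for unordered categories. Say which class the individual symptom items belong to.

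The cost is a few sentences: no extra participants, data or visits. The Trial status section reports recruitment under way and no one through treatment when the article was submitted, so at that stage the change could still precede any analysis.

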### Assignment and blinding

Block randomization is conducted in a 1:1 ratio to receive either Yirui capsules or the placebo. As this study is a multicenter study, blocked randomization is conducted for each center. The randomization sequence table generated by Statistical Analysis System (SAS) Version 9.2 was provided by a specific statistical researcher who does not participate in the clinical trial. The statistical researcher randomly distributes the number to the research products. The random numbers are kept in opaque sealed envelopes and sent to research centers. Afterwards, clinical investigators randomly assign the random number based on enrollment order and provide the corresponding drug. Choosing the number intentionally is strictly forbidden. The random number is fixed during the whole study. The blinding base containing the randomization sequence, parameters of sequence, and random number is sealed in duplicate and reserved by the principal investigator and product registration applicant. Patients and clinical investigators can only be aware of the individual random number. Treatment assignments are not exposed and are blinded to patients and any clinical investigators involved in this trial until the entire study is completed. At the last visit, all participants and clinical investigators will finish a questionnaire about which treatment (Yirui capsule group or placebo group) the patients received to assess the success of blinding. Emergency letters containing random number and treatment assignment would also be prepared by a specific statistical researcher. Code breaks are only allowed in emergency situations when practical intervention is compulsory for further management of the participant.

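### Secondary outcomes are compared by two-sample tests with no baseline covariate and with centre excluded, which gives up precision at no benefit

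*Protocol article*

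**What the plan says.** Four statements in the protocol article bear on this point.

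- Outcomes: "Secondary outcomes include the mean changes from baseline at treatment endpoint in LDL-C, TC, TG, HDL-C, apoA, apoB, non-HDL-C, SF-36 scoring", followed by the symptom scale and BMI. The same section has the lipid profile and scales taken at every visit, so each variable has a week-0 value.
- Statistical analysis, between-group test: "Efficacy difference between groups will be assessed with the utilization of the two-sample *t* test or corresponding non-parameter methods for quantitative variables". No covariate is named.
- Statistical analysis, centre: "a covariance model is used to evaluate the center effect for the primary variable", and then "Other secondary outcomes will take no account of the center effect".
- Assignment and blinding: "Block randomization is conducted in a 1:1 ratio to receive either Yirui capsules or the placebo" and "As this study is a multicenter study, blocked randomization is conducted for each center". Centre, with four hospitals, is therefore a randomisation stratum.

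**The concern.** The trial balances the arms within each hospital and measures every secondary variable before treatment, but the planned between-group tests use neither fact as a covariate. The multicentre design is given as the reason for a covariance model on the primary variable. The other outcomes are exempted without a reason, although the same randomisation applies to them.

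Three things are at stake for LDL-C, TC, TG, apoB, SF-36 and the rest:

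- confidence intervals that may be wider than the data require;
- estimates that move with any chance difference between arms at baseline, with no pre-specified adjustment;
- a standard error that ignores the stratum and so is somewhat too large.

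The sample size was set on the binary primary outcome alone, so precision on the continuous outcomes was not planned for and is worth having.

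**Working it through.** The plan states no figure for these analyses, so there is none to reproduce. From the documents: 1:1 allocation, 90 per arm, two-sided 5% level. Not in the documents, and therefore assumed: the correlation ρ between baseline and week 24, the SD ratio k (baseline SD divided by week-24 SD), and the share c of outcome variance explained by centre.

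**1. Baseline as a covariate.** Set the week-24 SD to 1.

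- Variance of the change: 1 + k² − 2ρk.
- Residual variance after ANCOVA: 1 − ρ².
- Ratio, ANCOVA to change score: (1 − ρ²)/(1 + k² − 2ρk).

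The numerator is smaller than the denominator by (k − ρ)². So, apart from the few degrees of freedom spent, ANCOVA is never less precise, and the two are equal only when ρ = k. With k = 1 the ratio reduces to (1 + ρ)/2.

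| k | ρ | Ratio | Variance saving |
|---|---|---|---|
| 1 | 0.3 | 0.65 | 35% |
| 1 | 0.5 | 0.75 | 25% |
| 1 | 0.7 | 0.85 | 15% |
| 1 | 0.9 | 0.95 | 5% |
| 0.7 | 0.5 | 0.75/0.79 = 0.95 | 5% |
| 0.7 | 0.6 | 0.64/0.65 = 0.98 | about 2% |
| 0.7 | 0.7 | 0.51/0.51 = 1.00 | 0% |

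For k = 1, if the change-score test had 80% power, ANCOVA at the same sample size would have 93.5%, 89.9%, 86.0% and 82.0% for ρ = 0.3, 0.5, 0.7 and 0.9.

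**2. Chance imbalance.** With 90 per arm, the standard error of the baseline difference is √(2/90) = 0.149 SD. With k = 1 and ρ = 0.5, the change-score difference shifts by (1 − 0.5) × 0.149 = about 0.07 SD for an imbalance of one standard error, and by about 0.15 SD for two. ANCOVA removes this shift.

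**3. Leaving out centre.** With balanced blocks within centre, the true variance of the treatment difference is about (1 − c) times the variance that the unadjusted test estimates. Actual type I error = 2 × [1 − Φ(1.96/√(1 − c))].

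| c | Actual type I error | Power where the centre-adjusted test has 80% |
|---|---|---|
| 0% | 5.0% | 80.0% |
| 1% | 4.9% | 79.7% |
| 5% | 4.4% | 78.5% |
| 10% | 3.9% | 76.9% |

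**The case against.** The strongest reply is that nothing here is invalid, and that stands. Three stronger readings are tempting, and the documents do not support them.

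- A reader might infer that the plan throws the baseline value away. It does not: the outcomes are changes, so baseline enters by subtraction. Only adjustment for it as a covariate is missing.
- A reader might infer bias or a risk of false positives. Randomisation keeps the comparison unbiased on average. Regression to the mean acts on both arms alike and matters only through chance imbalance. Ignoring the stratum errs on the conservative side.
- A reader might take the 15% to 25% saving for ρ = 0.7 to 0.5, equivalent to 90/0.85 = 106 up to 90/0.75 = 120 per arm, as the established size. That needs equal SDs at both times. The entry criteria select on lipid thresholds (LDL-C ≥3.37 mmol/L in one route, TG ≥5.65 mmol/L excluded), so baseline spread may be narrower than week-24 spread. At k = 0.7 the saving for the same correlations nearly vanishes. If k exceeds 1, it is larger than in the equal-SD case.

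It can also be said that an article names only a family of tests and leaves covariates to the analysis plan, and that the centre sentence may only limit where a centre effect is examined. The first has some force for baseline, which the text does not expressly exclude. But the named tests admit no covariates, and the sentence on centre is a stated choice: an analysis plan that adjusted the secondary outcomes for centre would contradict it on its plain reading.

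**Conclusion.** The point holds as a matter of efficiency. The planned comparison of the quantitative secondary outcomes is unbiased, but it leaves chance baseline imbalance unadjusted and is mildly conservative, with actual type I error of about 4.9% to 3.9% if centre explains 1% to 10% of variance. It also gives up precision by an amount that the documents do not allow to be fixed: 35% to 5% of the variance for ρ of 0.3 to 0.9 with equal SDs, and about 5% to 0% for ρ of 0.5 to 0.7 with k = 0.7. All of these figures rest on assumed values of ρ, k and c. The weight is low to moderate. No primary conclusion is touched, but the improvement is free.

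**What to change.** Delete the sentence that exempts the secondary outcomes from the centre effect. For each quantitative secondary outcome, specify an ANCOVA of the week-24 value or of the change, with treatment, centre and that variable's baseline value as terms, and report the adjusted difference with its 95% CI.

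A log scale for TG, a repeated-measures model and centre-stratified (van Elteren) tests for ranked symptom items are optional. A repeated-measures model would have to be reconciled with the last-observation-carried-forward rule.

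The cost is wording only, with no new patients, visits or measurements. Because the exclusion stands in the protocol, correct it there as well as in the analysis plan. When the article was submitted, no participant had completed treatment, and allocation stays blinded until the study ends. If made before unblinding, the change cannot be driven by knowledge of the treatment results.
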